### Economic evaluation

For the health economic analysis, intervention costs will be calculated using available data on staff costs, incentives, on-costs, other overheads, and activity levels. These will be added to the costs of other health and social care services derived from the Client Service Receipt Inventory and records combined with nationally applicable unit costs (e.g. Curtis [45]). Cost comparisons at 3 and 18 months will be made using regression models, with bootstrap methods used to generate confidence intervals around the cost differences. Cost-effectiveness from an NHS perspective at 3 and 18 months will use three outcome measures: number of cannabis-negative urine samples, days of reported cannabis abstinence and QALYs (derived from the EQ-5D with SF-12 QALYs used in secondary analyses)). If, for any of these the intervention has higher costs and better outcomes than usual treatment, then cost-effectiveness will be expressed in the form of incremental cost-effectiveness ratios, estimated by dividing the incremental costs by the incremental benefits of the intervention. Uncertainty around cost-effectiveness estimates will be explored using cost-effectiveness planes (through generating a large number of cost-outcome combinations using bootstrap methods) and cost-effectiveness acceptability curves (showing the probability of the intervention being cost-effective at various levels of willingness to pay for health benefits). The range of values for QALYs will be £0 to £100,000 so as to include the threshold used by NICE. The values for the other measures will be chosen so that the points at which one arm has 50 %, 60 %, 70 %, 80 %, and 90 % of being the most cost-effective can be observed. It will then be a value judgement as to whether these values are acceptable. Cost-effectiveness will be investigated regardless of clinical outcome.

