**Methods:**

CIRCLE is a two-arm, rater-blinded randomised controlled trial (RCT) investigating the clinical and cost-effectiveness of a CM intervention for reducing cannabis use among young people receiving treatment from UK Early Intervention in Psychosis (EIP) services. EIP service users (*n* = 544) with a recent history of cannabis use will be recruited. The experimental group will receive 12 once-weekly CM sessions, and a voucher reward if urinalysis shows that they have not used cannabis in the previous week. Both the experimental and the control groups will be offered an Optimised Treatment as Usual (OTAU) psychoeducational package targeting cannabis use. Assessment interviews will be performed at consent, at 3 months, and at 18 months. The primary outcome is time to relapse, defined as admission to an acute mental health service. Secondary outcomes include proportion of cannabis-free urine samples during the intervention period, severity of positive psychotic symptoms, quality-adjusted life years, and engagement in work or education.

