## Methods/design

### Design

CIRCLE is a rater-blind, randomised controlled trial with two arms (Fig. 1). The experimental group will receive a 12-week CM intervention, as well as a manualised psychoeducational intervention delivered by clinical staff, which represents an Optimised version of Treatment as Usual (OTAU) that is offered by EIPs in the management of cannabis misuse. The control group will receive OTAU only. Assessments will be performed at the time of consent, 12 weeks following consent (at the end of the intervention period), and at 18 months following consent. The primary outcome is time to relapse, operationalised as admission to an acute mental health service.

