### Contingency management

The CM intervention offers financial incentives contingent on urinalysis results indicating cannabis abstinence. The intervention voucher schedule and rules are adapted from Budney et al. [28, 29], which offered a voucher-based CM intervention for treatment of cannabis dependence in the general population. The intervention comprises 12 once-weekly urinalysis sessions and will be delivered by EIP clinicians. At each session, the participant will be required to provide a urine sample. A temperature strip on the side of the specimen cup will allow the EIP staff to check whether the sample has been tampered with. In week 1 of the intervention, details of the intervention will be explained to the participant, and they will be asked to sign an ‘abstinence contract’ indicating that they understand and accept its rules, and agree to abide by the test results. In the first week, participants will receive a £5 voucher for attending and providing a urine specimen independent of the drug test results, which provides a ‘baseline’ result. From week 2 to week 12, participants will receive vouchers, increasing by £5 every 2 weeks, contingent upon producing negative specimens. Vouchers will be for a local supermarket. Participants who abstain from cannabis use for the full duration of the intervention will earn £240.

Urinalysis will be performed using a small benchtop analyser capable of providing rapid test results of drug misuse urinary concentration (Kaiwood CHR-110). To perform the analysis, the EIP staff member pipettes a fixed amount of urine into a buffer solution tube to give a 7:1 serial dilution. This allows a standard 50-ng/ml marijuana test cassette placed in the analyser to provide a urinary cannabis concentration reading between 0 and 350 ng/ml. Guidelines will be provided to the EIP staff to allow interpretation of the test results, whereby a sufficient drop in urinary tetrahydrocannabinol (THC) concentration will be taken as indicative of abstinence since the previous urinalysis session. These guidelines are based on published data regarding the urinary half-life of cannabis [30].

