**Fig. 2 Fig2:**
[figure not shown]
Standard Protocol Items: Recommendations for Interventional Trials (SPIRIT) figure. Overview of the schedule of events

Cannabis use○ The Time Line Follow Back (TLFB) [34] will be used to record self-reported cannabis use over the last 6 months. The TLFB is a retrospective calendar-based measure of daily substance use, with good test-retest reliability demonstrated for cannabis [35]. This will be used to establish eligibility in terms of cannabis use and extent of recent use○ Structured Clinical Interview for the *Diagnostic and Statistical Manual of Mental Disorders, version 4* (DSM-IV) (SCID) part E will be used to assess history of alcohol and substance misuse disorders○ Specimens for urinalysis will be obtained with the threshold set at a level for detecting cannabis use in the previous 28 days (i.e. 50 ng/ml cannabis metabolites)
Psychotic symptoms○ The positive and negative subscales of the Positive and Negative Syndrome Scale (PANSS) [36]. The PANSS is a well-established measure of psychotic symptoms, with strong psychometric properties in terms of validity, reliability, and sensitivity [37]
Service use and health economic analysis○ Client Service Receipt Inventory (CSRI), developed originally by Beecham and Knapp [38] will be used to record clinical service use, medication use, receipt of state welfare, and use of other state-funded services including criminal justice services○ The 12-Item Short Form Survey (SF-12) [39] and the EuroQoL, 5 dimensions (EQ-5D) questionnaire [40] are widely used measures of health status with good psychometric properties [41, 42], which will be used to derive quality-adjusted life years’ (QALYs) data

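### The economic outcome counting cannabis-negative urine samples is not limited to samples taken in both arms, and the abstract's intervention-period proportion has almost no control-arm counterpart

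*Protocol article*

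**What the plan says.** All references are to the protocol article.

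- **Economic evaluation.** "Cost-effectiveness from an NHS perspective at 3 and 18 months will use three outcome measures". The list opens with the urine count, "three outcome measures: number of cannabis-negative urine samples"; the others are days of reported abstinence and QALYs. The section does not name the samples to be counted. It also says that cost-effectiveness will be examined whatever the clinical result.
- **Abstract, Methods.** "Secondary outcomes include proportion of cannabis-free urine samples during the intervention period".
- **Secondary outcomes.** The main-text list has no such proportion. Its urine outcome is the urinalysis result at follow-up.
- **Contingency management.** "The intervention comprises 12 once-weekly urinalysis sessions and will be delivered by EIP clinicians". The Interventions section gives CM to the experimental group alone, and under Design, "The control group will receive OTAU only". The description of OTAU includes no urine testing.
- **Assessment interviews and Outcome measures.** Both arms are assessed at consent, 12 weeks and 18 months, and urinalysis is among the measures taken at every assessment.
- **Rule for a negative result.** For the weekly CM sessions, guidelines apply "whereby a sufficient drop in urinary tetrahydrocannabinol (THC) concentration will be taken as indicative of abstinence since the previous urinalysis session". For the assessments, "Specimens for urinalysis will be obtained with the threshold set at a level for detecting cannabis use in the previous 28 days", given as 50 ng/ml.

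**The concern.** A count of negative results depends on how often a person is tested as well as on how often they abstain. Here the testing schedule differs by arm because the testing is itself part of the experimental treatment. If the economic count takes in the weekly samples, the CM arm has many more chances to score. The excess goes straight into the effect difference, which is the denominator of the incremental cost-effectiveness ratio, and from there into the acceptability curve. A trial with no effect on cannabis use could then report a finite cost per additional negative sample.

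The abstract's proportion has a related problem. It is defined over a period in which one arm is tested weekly and the other is not. It also disagrees with the outcome list in the body of the same article.

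A second difference lies beneath both. A weekly CM sample is judged by its fall from the previous session, whereas an assessment sample is judged against a fixed threshold. The discussion under Strengths and limitations accepts that a one-week fall can come from reduced use, so that a participant may be rewarded in the short term while still using. Pooling the two sources would combine two different outcomes, one of which exists in one arm only.

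**Working it through.** The plan gives no figure for this outcome, so there is none to reproduce. The check counts scheduled samples per arm and works out what each reading yields when treatment has no effect.

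**Inputs**
- Weekly CM sessions: 12 in the CM arm (Contingency management), none described for controls (Design, Interventions).
- Post-baseline assessment samples in each arm: 1 by 3 months and 2 by 18 months (Assessment interviews, Outcome measures).
- Probability p that a sample is negative: not given in the article. Assumed equal in both arms (no effect), with a range of 0.20 to 0.40.

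**Scheduled post-baseline samples per person**

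| Reading | By 3 months, CM v control | By 18 months, CM v control |
|---|---|---|
| All samples | 12 + 1 = 13 v 1 | 12 + 2 = 14 v 2 |
| Assessment samples only | 1 v 1 | 2 v 2 |

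**Expected difference with no effect** = p × (CM samples − control samples)

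- All samples: 13 − 1 = 12 and 14 − 2 = 12, so the difference is 12p at both times.
- All samples except week 1: 11p. The Contingency management section treats week 1 as a baseline reading and pays for it whatever the result. There is no earlier session for it to have fallen from, so under the weekly rule at most 11 weekly samples can qualify.
- Assessment samples only: 1 − 1 = 0 and 2 − 2 = 0, so the difference is 0 for every p.

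| p | 11p | 12p | Assessment only |
|---|---|---|---|
| 0.20 | 2.2 | 2.4 | 0 |
| 0.30 | 3.3 | 3.6 | 0 |
| 0.40 | 4.4 | 4.8 | 0 |

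At p = 0.30 with all samples counted, for example, the expected counts by 3 months are 13 × 0.30 = 3.9 and 1 × 0.30 = 0.3, a gap of 3.6 that owes nothing to treatment.

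These are scheduled maxima. Missed sessions and the two permitted holiday weeks would lower the CM counts without removing the imbalance.

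**The abstract's proportion.** A proportion does not grow with the number of samples, so the count artefact above does not carry over to it. The comparison is still unlike with unlike. In the CM arm it would be formed from up to 12 weekly results under the fall-in-concentration rule. In the control arm it would rest on one result at the end of the period under the fixed threshold.

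**The case against.** The strongest reply is that the economic outcome, read with the rest of the article, already means the assessment samples. Its time points are those of the follow-up assessments, urine is taken from everyone there, and the Secondary outcomes section names urinalysis at follow-up. Nothing in the article says that weekly CM readings enter the economic analysis. On that reading the comparison is 1 v 1 and 2 v 2 and is unbiased under no effect. One may add that a journal article leaves such definitions to the fuller analysis plan it promises.

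Much of this stands. A reader might infer that the economic outcome cannot be compared between arms, or that it favours CM by construction. The article supports neither: a comparable measure is available from samples already planned, and the bias arises only if weekly samples are counted. Nor is it right that the abstract's proportion has no control-arm value whatever, since Design places the 12-week assessment at the end of the intervention period.

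The magnitude is also open to challenge. The range for p is an assumption, and one p for both sample types sits awkwardly beside the point that they define a negative differently. The figures therefore show the size of the artefact and do not predict it.

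Two things remain. The abstract and the Secondary outcomes section disagree in current text, which is not detail deferred to another document. And a number of samples is an odd description of what would be a single yes/no result at 3 months; the word fits the weekly series better, as does the abstract's reference to the intervention period. The economic wording therefore leaves open a reading that is biased.

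**Conclusion.** The point holds in a limited form. The abstract names a between-arm outcome for which controls have at most one sample, and which differs from the main-text list. The economic count is not restricted to samples taken in both arms.

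If weekly CM samples were included, the measure would show a gain of about 11p to 12p negative samples per person at both 3 and 18 months with no true effect. That is 2.2 to 4.8 for an assumed shared p of 20% to 40%, before missed sessions, and it would mix two rules for a negative result. If only assessment samples are used, the null difference is 0.

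Severity is moderate. One of three economic measures and one secondary outcome named in the abstract are involved. The primary outcome, the QALY analysis and days of reported abstinence do not depend on the urine schedule.

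**What to change.** 1. In Economic evaluation, define the urine measure as the assessment sample negative at the already specified 50 ng/ml threshold, at 12 weeks and at 18 months, in both arms, and state that weekly CM readings are excluded.
2. In the abstract, replace the intervention-period proportion with the urine outcome in the Secondary outcomes section. If the article can no longer be changed, record in the analysis plan that the main-text list governs.
3. Report the weekly CM results for the CM arm only, as process data, stating the rule by which a sample was called negative.

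The cost is wording alone, as the assessment samples are already planned in both arms. It should be settled before anyone sees outcome data, because the choice of samples could by itself decide whether this measure shows a gain.

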## Discussion

The present study is a rater-blinded RCT investigating the clinical and cost-effectiveness of CM for reducing cannabis use in EIP patients with a history of recent cannabis use. Cannabis is a significant issue in this population. Rates of cannabis use among people with first-episode psychosis are high, resulting in poorer clinical, social, and functional outcomes, and greater clinical service use. However, there is little evidence for any effective interventions for comorbid substance misuse in established psychosis. If CM is found to be clinically and economically beneficial, it will offer strong support for using such interventions to reduce cannabis use among EIP service users.

### Strengths and limitations

With a recruitment target of 544 participants, CIRCLE is one of the largest trials of CM worldwide. To the best of our knowledge it is also the first RCT of CM specifically for cannabis use in psychosis, although there are a number of related studies. Bellack et al. [23] trialled CM for substance use in psychosis, including cannabis, cocaine, or heroin, which required participants to test negative from the first session. Sigmon et al. [24, 25] performed two small feasibility studies of CM for cannabis use in psychosis, but used within-subject designs rather than a RCT design. Participants are followed over a relatively long period of 18 months in accordance with NICE recommendations for future research for psychosocial interventions for substance misuse in psychosis [46]. The rationale for targeting EIP patients in particular is that there is also good reason to believe that motivation to change patterns of cannabis and other substance use is high in this cohort [15]. Secondly, EIP is a form of secondary preventative care [47], with the aim of preventing or attenuating the risk of relapse to improve long-term prognosis. Given the substantial evidence base linking cannabis use to higher rates of relapse, reducing cannabis use in EIP services is consistent with EIP aims.

One potential concern regarding the use of CM interventions in publicly funded health services is its acceptability to the public, clinicians, and service users. A mixed-method substudy to the main trial to explore this topic is planned. However, there is already some evidence that public opinion is in favour of CM for treatment adherence in severe mental illness [48]. Potential concerns about the use of financial incentives were also carefully considered in the design of the CIRCLE intervention. The design is based on Budney et al. [28, 29] and feedback on it was sought from service users, pilot study participants, carers, and clinical teams before and after the pilot study through focus groups and one-to-one interviews.

One technical issue for CM for cannabis use is the relatively long effective half-life of cannabis. Conventional marijuana urinalysis tests could not be used for the CM, as a positive urine result may be related to cannabis use that had taken place more than 1 week previously. Use of such tests would delay the initiation of treatment by up to 4 weeks to allow a participant’s urinary THC level to fall below 50 ng/ml. To address this, CIRCLE uses desktop analysers capable of providing a urinary THC concentration reading. As discussed, a reduction in urinary THC in line with trial guidelines will be taken as evidence of abstinence. However, it is possible that a reduction in urinary THC over a 1-week period could occur due to a reduction in cannabis use rather than abstinence. As such, it is possible that participants can receive the voucher reward while still using in the short term. However, medium and long-term trends, detectable over two or three sessions, will clearly indicate abstinence rather than reduction of cannabis use as urinary THC will not continue to decline or fall to below 50 ng/ml. Participants will be informed that they will need to abstain fully throughout the intervention period to receive all the voucher rewards.

### Trial status

The pilot phase of CIRCLE began on 1 January 2012 and ended on 28 February 2013. Approval to proceed to the full trial was received in April 2013 and recruitment to the main trial is currently ongoing. The end date for CIRCLE is 31 October 2017.

## Abbreviations

CBT: Cognitive behavioural therapy
CM: Contingency management
EIP: Early Intervention in Psychosis
MI: Motivational interviewing
NICE: National Institute for Health and Care Excellence
OTAU: Optimised Treatment as Usual
RCT: Randomised controlled trial
